#### Remote Participation

All the procedures are identical to those followed during in-person participation, apart from the interactions with the serious game that are done remotely from their home using their personal computers.

### Participant Selection

The eligibility criteria were reviewed by a member of the research team before assignment to the study. Textbox 1 lists the inclusion and exclusion criteria for enrollment into the study.

Inclusion and exclusion criteria for participant enrollment.
**Inclusion criteria**
Participants should be between 7 and 16 years old.Participants of the attention deficit hyperactivity disorder (ADHD) group should be diagnosed by an approved body of the Ministry of Health.Participants should be willing to follow the study protocol and procedures.The ADHD symptoms should not be attributed to organic disease.Parents must voluntarily provide written consent for their child’s participation in the study.

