**Objective:**

To address the challenges of existing procedures for ADHD diagnosis, the ADHD360 project aims to develop a platform for (1) early detection of ADHD by assessing the user’s likelihood of having ADHD characteristics and (2) providing complementary training for ADHD management.

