**Conclusions:**

ADHD360 is characterized by its notable capacity to discriminate player gameplay behavior as either ADHD or non-ADHD. Therefore, the ADHD360 platform could be a valuable complementary tool for early ADHD detection.

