## Introduction

### Background and Objectives

Attention deficit hyperactivity disorder (ADHD) is one of the most common neurodevelopmental disorders during childhood [1]. ADHD is commonly diagnosed during childhood and prolongs into adulthood to a variable extent ranging from 5% to 75% [2]. ADHD is characterized by persistent symptoms of inattention and hyperactivity/impulsivity that interfere with or attenuate social, academic, and occupational functioning, as well as the developmental stage. The symptoms are present prior to the age of 12 years, for a period of at least 6 months in 2 or more settings [3].

The diagnosis procedure remains challenging, as it is nonstandardized, multiparametric, and highly dependent on subjective evaluation of the perceived behavior [4,5]. Additionally, the effectiveness of treatment strategies commonly relies on systematic monitoring using pen-and-paper methods [4,6]. Subjectivity bias, difficulty monitoring in different settings, and risk of data loss are inherent obstacles to these methods.

To address the limitations of the existing approaches, ADHD360 focuses on developing an integrated technology solution that includes a serious game for a probabilistic prediction indicating the presence of ADHD in players using machine learning (ML) models and a mobile app for monitoring ADHD behaviors. The platform aims to (1) facilitate early detection of ADHD characteristics and (2) serve as an adjunct intervention for ADHD management. The first goal of the project is to analyze the gameplay behavior of the users with respect to their diagnosis (ie, ADHD or non-ADHD). Thus, discriminative gameplay patterns among the groups (ADHD or non-ADHD) are explored to estimate the users’ likelihood of having ADHD characteristics. The second goal is to investigate the effectiveness of the platform as an intervention for ADHD management.

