**Exclusion criteria**
Participants suffering from comorbid conditions other than ADHD are excluded.Children whose parents are not willing to provide written consent for participation in the study are excluded.

All participants are comprehensively informed regarding the procedures of the study through a document named “Participant Information and Consent Form.” Moreover, the participants are informed about the purpose of the study as well as the following aspects of their participation:

Their participation is voluntary.They can ask questions about the study procedures before participating in the study.They will be aware of the underlying risk or burden associated with their participation.They will know who will benefit from conducting this research.They will know how data collection and data protection will be performed during the project’s lifetime as well as whether data will be destroyed or reused (in case there is a possibility to reuse them).They will be fully informed, and they will agree for further use of their data.They can leave the study at any time and withdraw their data from the study.They will be aware of the possible commercial exploitation of the research findings.

Each informed consent is signed by the researcher who informs the participant and the principal investigator of the study. The informed consent explicitly states that the study was approved by the Committee for Bioethics and Ethics of the Medical School at the Aristotle University of Thessaloniki and all personal details are anonymized using a unique user identification code.

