## Results

### Demographics

In total, 43 participants were recruited with a mean age of 11.82 (SD 2.81) years. Among these, 28 (65%) were male and 15 (35%) were female. Of the 43 participants, 18 (42%) were diagnosed with ADHD and 25 (58%) participants were considered controls (non-ADHD). Approximately 30 participants (70%) completed the first part of the pilot phase remotely.

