## Discussion

Limitations of the existing screening procedures for ADHD diagnosis are summarized as high dependence on pen-and-paper practices, subjectivity bias, difficulty in monitoring in different settings, and risk of data loss. The ADHD360 platform, consisting of the serious game “Pizza on Time” and the mADHD360 app, attempts to offer a holistic technological solution for early detection of ADHD characteristics and serve as a training tool against ADHD-related symptoms. It facilitates real-time data collection in different settings and from different individuals involved in the user’s care. Moreover, the ADHD360 platform enables quantitative data analysis assessing the behavior and game performance of the user while providing a more integrated view of the user's behavioral characteristics. Investigating different state-of-the-art ML methods revealed that our platform is characterized by a notable capacity to discriminate players based on their in-game patterns as those who have ADHD characteristics and those who do not. Thus, it is expected to serve as a complementary screening tool benefiting health care professionals, educators, and people with ADHD.

However, the health emergency imposed by COVID-19 affected the implementation of pilot trials by forcing adaptation of the protocol to remote conditions. Moreover, lockdowns and social distancing may have contributed to the low sample size and the high number of dropouts during the study. Additionally, the long duration of the experimental protocol and the need for commitment to the study procedures may have negatively affected users’ adherence to pilot trials. Moreover, ADHD has been characterized by “a dislike of mental effort” [45]. Considering the aforementioned limitations, we recruited about twice as many participants as originally intended. However, the dropout rate was approximately 30% (13 participants), as 30 participants (70%) completed the first part of pilot phase remotely.

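### Early detection and screening use are inferred from a known-groups pilot, which can show only discrimination between diagnosed cases and children without a diagnosis

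*Protocol article*

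**What the plan says.** The Abstract's Objective gives the platform's first purpose as "early detection of ADHD by assessing the user’s likelihood of having ADHD characteristics". The Abstract's Conclusions move from discrimination of gameplay to the statement that "the ADHD360 platform could be a valuable complementary tool for early ADHD detection", and the Discussion adds that "it is expected to serve as a complementary screening tool benefiting health care professionals, educators, and people with ADHD".

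The study behind these statements is set up as follows.

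- **Cases.** The inclusion criteria state that "Participants of the attention deficit hyperactivity disorder (ADHD) group should be diagnosed by an approved body of the Ministry of Health". Recruitment of Participants says that they come mainly from one community mental health centre.
- **Both groups.** The exclusion criteria state that "Participants suffering from comorbid conditions other than ADHD are excluded".
- **Case share.** Recruitment of Participants planned at least 10 children per group. Demographics reports 18 with ADHD and 25 controls.
- **Label.** ML Methodology trains the classifiers on the player's known status. It then takes test-set performance as the estimate of how the system will perform in general on data without labels.

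The Introduction states the first goal more narrowly: to examine gameplay in relation to the existing diagnosis and to look for patterns that separate the two groups.

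**The concern.** Detecting ADHD early means identifying it in a child whose status is not yet settled. Here every case has already been through the diagnostic process, and that prior diagnosis is the label that the model learns. The article describes no group that is enrolled with status unknown and then given a reference diagnosis, and no follow-up to a later diagnosis. A symptomatic child without a diagnosis cannot enter as a case. Nothing listed bars such a child from the non-ADHD group, where the model would be taught to call that child negative. A larger sample of the same kind would not change this.

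A second problem concerns the performance figures. Accuracy, precision and F1 depend on the proportion of cases among those tested. That proportion was fixed by recruitment, so the figures do not describe use in a population where ADHD is less common. A public release of the game is planned, and families or educators could read a positive result as a screening result.

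**Working it through.** **Inputs.** Demographics: 18 ADHD and 25 controls. Table 4, SVM row (the selected model): accuracy 0.85, precision 0.75, recall 1.00, F1 0.85. Table 4, NB row: accuracy 0.42, precision 0.42, recall 1.00, F1 0.60. The article gives no prevalence for a screening population, so 5%, 10% and 20% are assumptions.

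**Case share.** 18/43 = 0.419, which reproduces the stated 42%. The planned share was 10/20 = 50%.

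**Counts behind the SVM row.** Recall 1.00 means no false negatives. Precision 0.75 means true to false positives of 3:1. With 3 true positives, 1 false positive and 3 true negatives:

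- accuracy = 6/7 = 0.857
- precision = 3/4 = 0.75
- F1 = 2×3/(2×3 + 1 + 0) = 6/7 = 0.857

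These match Table 4 if decimals are truncated. No table with 8 children fits: 3 true positives, 1 false positive and 4 true negatives give accuracy 7/8 = 0.875, and 6 true positives with 2 false positives give 6/8 = 0.75. The NB row confirms the split: calling all seven positive gives accuracy and precision 3/7 = 0.428, and F1 = 6/10 = 0.60. The test set therefore appears to hold 3 cases and 4 controls, a share of 3/7 = 43%. Gameplay Data states 8 test participants. That is a separate matter, to be reconciled with Table 4.

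**Sensitivity and specificity (exact 95%, Clopper-Pearson).**

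- Sensitivity 3/3 = 1.00, interval 0.29 to 1.00 (lower limit 0.025^(1/3) = 0.292)
- Specificity 3/4 = 0.75, interval 0.194 to 0.994

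**Precision at another prevalence p.** PPV = sens×p / (sens×p + (1 − spec)×(1 − p)). The range holds sensitivity at 1.00 and uses the two specificity limits.

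| Case share p | PPV at spec 0.75 | Range from specificity interval |
|---|---|---|
| 3/7 (test set) | 0.750 (the reported precision) | – |
| 20% (assumed) | 0.20/(0.20 + 0.25×0.80) = 0.50 | 0.24 to 0.98 |
| 10% (assumed) | 0.10/(0.10 + 0.25×0.90) = 0.31 | 0.12 to 0.95 |
| 5% (assumed) | 0.05/(0.05 + 0.25×0.95) = 0.17 | 0.06 to 0.89 |

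At 10% the limits are 0.10/(0.10 + 0.806×0.90) = 0.12 and 0.10/(0.10 + 0.0063×0.90) = 0.95. If sensitivity is also allowed to fall to 0.29, the lower end drops to 0.04.

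**Accuracy at another prevalence.** Accuracy = sens×p + (1 − spec share of errors removed), that is sens×p + spec×(1 − p). At 3/7 this is 3/7 + 0.75×4/7 = 0.857. At an assumed 10% it is 0.10 + 0.75×0.90 = 0.775, whereas calling every child negative would give 0.90.

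**The case against.** The best defence is that this is a pilot, and that comparing known groups is a normal first step for a classifier. The Introduction already words the operational goal as discrimination with respect to diagnosis. The Abstract's conclusion also begins with discrimination and is hedged, and the analysis is called preliminary, with a larger data set asked for. Accuracy is the figure in the Abstract. Precision appears only in Table 4, where recall is also shown, and no sentence applies the 0.75 to screening.

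Most of this stands, and it lowers the severity. It does not remove the point. The Abstract's conclusion still derives early detection from discrimination, the Discussion still expects screening use, and ML Methodology still treats the test-set result as general performance. The Discussion names sample size, dropout and remote conduct as limitations, but not known-group sampling, case mix or the recruited case share. The remedy that it offers, more participants, does not help unless the type of participant changes.

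It is also fair to object that projected PPVs from seven children say little. They do, which is why they belong only with their uncertainty.

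**Conclusion.** The point holds at moderate severity. The study can show that gameplay separates children with an existing ADHD diagnosis from comorbidity-free children without one. It cannot show detection before diagnosis. Its accuracy and precision belong to a case share of about 43%. For any prevalence below that, precision falls if sensitivity and specificity stay the same. The size of the fall depends on the assumed prevalence and is very uncertain: about 0.31 at 10%, range about 0.12 to 0.95. The counts are inferred from Table 4 and are not stated in the article.

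A reader might infer more, but the documents do not support it:

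- **That symptomatic undiagnosed children are excluded altogether.** They are kept out of the case group only.
- **That the two ends of the spectrum are compared, so performance must be inflated.** No severity threshold is set, and Table 2 total scores overlap: 18.60 + 10.62 = 29.22 is one SD above the non-ADHD mean, and 33.80 − 9.94 = 23.86 is one SD below the ADHD mean. Optimism is possible but not demonstrated.
- **That the cases are too old for early detection.** The statement that "The symptoms are present prior to the age of 12 years, for a period of at least 6 months in 2 or more settings" concerns the onset of symptoms. The mean age of 12.90 years comes from 10 of the 18 cases and says nothing about when they were detected.
- **That the article should report results for younger or recently diagnosed children, or time since diagnosis.** With three test cases such subgroups cannot be estimated, and that level of data-collection detail is commonly left to the full protocol.

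**What to change.** 1. In the Abstract's Objective and Conclusions and in the Discussion, restrict the study aim and the claims to discrimination of children with an existing ADHD diagnosis from comorbidity-free children without one, in line with the goal already stated in the Introduction. Leave early detection and screening to a later study that enrols children whose status is not yet known.
2. Add known-group sampling, case mix and the recruited case share to the limitations. Qualify the sentence in ML Methodology on general performance accordingly.
3. Beside accuracy, report sensitivity and specificity with exact intervals, and label accuracy, precision and F1 as specific to the recruited case share.
4. Give a projected PPV, if any, only over a stated range of assumed prevalence and with its uncertainty.

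The cost is rewording and a short recalculation from the test-set counts, with no new data. The downside is a less favourable stated claim.

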**Results:**

A total of 43 participants were recruited for this study, where 18 were diagnosed with ADHD and the remaining 25 were controls. Initial neuropsychological assessment confirmed that the participants in the ADHD group showed a deviation from the participants without ADHD characteristics. A preliminary analysis of collected data consisting of 30 gameplay sessions showed that the trained ML models achieve high performance (ie, accuracy up to 0.85) in correctly predicting the users’ labels (ADHD or non-ADHD) from their gameplay session on the ADHD360 platform.

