#### ML Methodology

State-of-the-art ML algorithms are used to analyze labeled gameplay data. Specifically, we attempt to classify game-generated data based on the user’s known label (ADHD or non-ADHD). All in-game events of a gameplay session are recorded to form a time series that one can use to reconstruct the whole gameplay session. These events correspond to player actions and environmental parameters, such as performing a jump/move, left or right moving action, obstacle collision, and coin collection. Informative feature extraction is performed by splitting players’ time series depending on the game level. Different feature extraction techniques are assumed for each level depending on its type. In the main runner game, several aggregates are calculated by capturing different events during the gameplay (ie, movement of a player or the ability to avoid obstacles). In the mini games, feature extraction is based on the characteristic game mechanics and events of the respective mini game. The final feature vector of each player is produced by concatenating the individual-level feature vectors.

A schema that includes train-test splitting with a 75:25 split ratio, *k*-fold cross-validation (CV) with k=3, an ML pipeline, and data evaluation was designed for experimental purposes. The train-test splitting is used for model specification (eg, feature selection and model tuning), model selection, and training of the final model. Modeling decisions are made on the training set. Thus, the test set is used only to evaluate and report the statistics of the algorithm’s performance. The purpose of 3-fold CV is to fine-tune the hyperparameters of the supervised learning algorithms (classifiers) that we investigate.

For each classifier, an ML pipeline was designed to include the following procedures: (1) removal of features with 0 variance, (2) univariate feature selection according to a statistical criterion (ANOVA *F* value between label and feature), (3) principal component analysis for dimensionality reduction, and (4) classifier training. Therefore, the hyperparameters of all the steps are tuned (eg, the number of components in principal component analysis) in the 3-fold CV process. The *F1* score is used as the optimization criterion in the 3-fold CV, and the best configuration of each method's pipeline is then used on the entire training set (fully trained pipeline).

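### The classifier's reference label is verified on the ADHD side only, so the study can claim to separate diagnosed from not-diagnosed children, not children with and without ADHD characteristics

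*Protocol article*

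**What the plan says.** - **ADHD label.** Inclusion criteria: "Participants of the attention deficit hyperactivity disorder (ADHD) group should be diagnosed by an approved body of the Ministry of Health".
- **Control label.** Neither the inclusion nor the exclusion list says how a control is established. The only clinical exclusion is "Participants suffering from comorbid conditions other than ADHD are excluded", which does not remove an undiagnosed child with ADHD symptoms. Demographics reports that "18 (42%) were diagnosed with ADHD and 25 (58%) participants were considered controls (non-ADHD").
- **Use of the label.** ML Methodology: "we attempt to classify game-generated data based on the user’s known label (ADHD or non-ADHD"). Training, tuning and scoring all take this label as the truth.
- **Symptom information collected.** In-Person Participation describes the parent-completed ADHD Rating Scale-IV and, later, a telephone call in which psychologist and parents agree which behaviours to monitor. Neither is given a part in eligibility or in confirming the label.
- **Target of the claim.** The abstract's Objective is "early detection of ADHD by assessing the user’s likelihood of having ADHD characteristics". Its Results say that "the participants in the ADHD group showed a deviation from the participants without ADHD characteristics". The Discussion says the platform can "discriminate players based on their in-game patterns as those who have ADHD characteristics and those who do not".

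**The concern.** The label records whether a child holds an official diagnosis. The claim concerns whether a child has ADHD characteristics. The two differ for an undiagnosed child with many symptoms, and the stated criteria would place such a child among the controls. The article's Literature Summary itself raises possible underdiagnosis, and recruitment ran partly through social and mass media.

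If such a child is flagged by the classifier, the flag counts as a false positive, although it is right for the stated target. If the child is in the training set, the classifier learns the wrong pattern for that target. Accuracy, precision and the implied specificity are then measured against something other than what the conclusion describes, in a test set so small that one child matters.

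**Working it through.** **Inputs** (Neuropsychological Data and Table 2). ADHD Rating Scale-IV total: ADHD group 33.80 (SD 9.94), n = 10; controls 18.60 (SD 10.62), n = 20; full group stated as 23.67 (SD 12.56). The article gives no cut-off marking ADHD characteristics, so the cut-offs below are assumptions chosen to show a range.

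**1. Reproducing the stated figure.** Mean = (10 × 33.80 + 20 × 18.60)/30 = 710/30 = 23.67. Sum of squares = 9 × 9.94² + 19 × 10.62² + 10 × (33.80 − 23.67)² + 20 × (18.60 − 23.67)² ≈ 4572. SD = √(4572/29) = 12.56. Both match, so Table 2 covers the same 10 and 20 children.

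**2. Overlap under a normal model.** Share of controls above c = 1 − Φ((c − 18.60)/10.62). Share of diagnosed children below c = Φ((c − 33.80)/9.94).

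| Cut-off c | Controls above | Of 20 | Diagnosed below |
|---|---|---|---|
| 23.9 (ADHD mean − 1 SD) | 31% | 6.2 | 16% |
| 26.2 (midpoint of means) | 24% | 4.7 | 22% |
| 28.8 (ADHD mean − 0.5 SD) | 17% | 3.4 | 31% |
| 33.8 (ADHD mean) | 8% | 1.5 | 50% |

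A gamma shape with the same mean and SD gives 26%, 21% and 9% at 23.9, 26.2 and 33.8.

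**3. Check without a distribution.** For nonnegative scores the maximum is at least the mean of squares divided by the mean. For the controls this is 18.60 + (10.62² × 19/20)/18.60 = 18.60 + 5.76 = 24.4. At least one rated control therefore scored about 24.4 or more, above the ADHD mean minus 1 SD (33.80 − 9.94 = 23.86). On the hyperactivity-impulsivity subscale the average control (8.80) already exceeds the ADHD mean minus 1 SD (15.30 − 6.58 = 8.72). The overlap does not depend on the normal model alone.

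**4. Are the rated children the gameplay children?** In Table 3, logistic regression has recall 0 and accuracy 0.5714, as it would if it called every child non-ADHD. That gives an ADHD share of 1 − 0.5714 = 0.4286, or 9 of 21. In Table 4, naïve Bayes has recall 1.00 with accuracy and precision 0.42, which fits 3 ADHD children of 7. Together that is about 12 ADHD children. Applying 0.4286 to the stated 22 and 8 gives 9.4 + 3.4, about 13. Only 10 ADHD children have ratings, so the two sets of 30 differ.

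**5. Weight of one label in the test set.** The SVM's accuracy 0.85, precision 0.75 and recall 1.00 fit 3 true positives, 1 false positive and 3 true negatives: 6/7 = 0.857, 3/4 and 3/3. This implies 7 children, whereas Gameplay Data states 8, so the count is inferred. With predictions held fixed, relabelling the flagged control gives 7/7 = 1.00, and relabelling a control that was counted correct gives 5/7 = 0.71. Either way one label moves accuracy by 0.14.

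**The case against.** **A quarter mislabelled?** A reader might infer from Table 2 that roughly a quarter of controls carry the wrong label. The documents do not support that. The 24% needs the midpoint cut-off, which appears nowhere in the article. Two near-equal normal curves 1.46 SD apart (15.2/10.41, pooled SD) put about 23% of each group beyond their midpoint, however accurate the labels are; the same line would put 22% of officially diagnosed children on the wrong side. Table 2 gives no individual scores. A raised parent rating is one informant's report, not a diagnosis. The scores are raw, and the rated controls are younger (10.65 against 12.90 years) and 45% female, against an all-male ADHD group. These objections stand.

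**No check at all?** That is also too strong. The article says eligibility was reviewed before assignment and calls the rated controls healthy. A condensed article may omit screening that the full protocol describes. What stands is that the printed criteria fix one group only, and that no collected symptom measure is given a role in the label.

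**Is the target really different?** The Introduction frames the first goal by diagnosis, and the abstract's Conclusions speak of ADHD or non-ADHD. In those places the wording matches the label. The abstract's Objective and Results and the Discussion do not, so the article is inconsistent on what is being separated.

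**Would a rating-based analysis make things worse?** Excusing only misclassified controls by their ratings could only improve apparent performance, and dropping high-rated controls makes the groups more extreme. Both points stand and limit the remedy. A cut-off chosen now cannot be called prespecified for results already reported.

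**Conclusion.** The concern holds in a limited form. The control label has no stated verification, and the claim moves from diagnosis status to ADHD characteristics. The study's own ratings undercut describing the controls as free of such characteristics: about 8% to 31% of the 20 rated controls lie above illustrative cut-offs from 33.8 down to 23.9 under a normal model, and at least one must score about 24.4 or more if scores are nonnegative.

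This range measures overlap on one parent-rated scale. It is not a mislabelling rate, it covers 20 of the 25 controls, and it cannot be applied to the classifier labels, because the gameplay set appears to hold at least two ADHD children without ratings. Nor does it show that the published accuracy is too high: one wrong control label could move it either way. The defect limits what the study may conclude; it does not invalidate the comparison of diagnosed with not-diagnosed children.

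**What to change.** 1. Word the conclusion, in the abstract and the Discussion, as separating diagnosed from not-diagnosed children, and describe the controls as not diagnosed.
2. For children with both gameplay and rating data, add a sensitivity analysis that leaves out controls above one fixed rating cut-off, in both training and scoring. Label it post hoc for the present data, show it beside the all-controls result, and note that it widens the contrast between groups.
3. Report the ratings of all test children in both groups, not only of misclassified controls, and state how many gameplay children have a rating.
4. In the definitive study, give the rating already collected at entry a prespecified role in checking the control label, with the cut-off fixed in advance.

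The wording change costs nothing. The sensitivity analysis needs no new data, but it loses controls from a small sample and is limited by incomplete ratings (30 of 43 recruited children, and an unknown number of gameplay controls). Checking controls in the definitive study may exclude some volunteers.
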